## 6 TREATMENT PLAN

Please refer to the study calendar ([Appendix 8](#)) for an overview.

After screening, eligibility determination and enrollment, subjects will receive daratumumab, carfilzomib, lenalidomide, and dexamethasone, in 28-day cycles until progression, unacceptable toxicity or subject withdraws consent. The total study enrollment period is expected to be 12-18 months. A subject is considered to have completed the treatment phase of the study 4 weeks (28 days) after the end of the last treatment cycle. Excluding long-term follow up, the treatment phase of the study will be completed once the last subject completes the 28-day safety follow-up visit. Subjects who have not progressed will be followed for progression for up to 2 years from the completion of the safety follow-up visit. Subjects who have progressed, or have been removed from treatment for another reason, will be followed for survival for up to 2 years from the completion of the safety follow-up visit. An attempt will also be made to follow ASCT subjects for progression.

A subject is considered to be off-treatment following a 28-day safety follow-up period after the last treatment. Long-term follow-up for survival will be 2 years from the end-of-treatment visit.

### 6.1 Study Procedures

#### 6.1.1 Screening Procedures

The screening period is 21 days in length. The screening period starts only after the patient has signed the informed consent form. Refer to the Schedule of Events ([Appendix 8](#)).

| Signed
Consent | Written
and
Medical
History | Informed | Obtained prior to any study-specific assessments                                                                                                                                                                                                                                             |
|---------------------------|------------------------------------------------|-----------------|----------------------------------------------------------------------------------------------------------------------------------------------------------------------------------------------------------------------------------------------------------------------------------------------|
|                           |                                                |                 | 

• Age, gender, ethnic background

• Details on myeloma diagnosis

• Details on prior cancer therapy, including start and stop dates, disease progression during or after therapy, as well as discontinuation due to toxicities

 |

|                                             |                                                                                                                                                                                                                                                                                                                   |
|---------------------------------------------|-------------------------------------------------------------------------------------------------------------------------------------------------------------------------------------------------------------------------------------------------------------------------------------------------------------------|
|                                             | 
 
• Previous and concurrent relevant diseases
 
• Current symptoms and/ or residual toxicities from prior therapies
 
                                                                                                                                        |
| Pregnancy Test (if applicable)       | FCBP must have two negative pregnancy tests (sensitivity of at least 50 mIU/mL) prior to starting study treatment. The first pregnancy test must be performed within 10-14 days prior to the start of study treatment and the second pregnancy test must be performed 24 hours before lenalidomide is prescribed. |
| Physical Examination and Vital Signs | 
 
• Body height and weight
 
• BSA
 
• ECOG Performance Status (Appendix 2)
 
• Blood pressure, pulse, temperature
 
• Physical examination
 
                                                                           |
| Cardiac evaluation                   | 12-lead ECG                                                                                                                                                                                                                                                                                                       |
| Echocardiogram                       |                                                                                                                                                                                                                                                                                                                   |
| Urinalysis                           | Urine bilirubin, glucose, hemoglobin, ketones, pH, protein                                                                                                                                                                                                                                                        |
| Hematology (CBC)                     | Hemoglobin, hematocrit, white blood cell (WBC) count; WBC differential, red blood cell count, platelets. WBC differential may be automated or manual as per institutional standards.                                                                                                                              |
| Clinical chemistry                   | Sodium, potassium, chloride, bicarbonate, BUN, creatinine, glucose, calcium, phosphate, magnesium, ALT, AST, alkaline phosphatase, total bilirubin, total protein, albumin, urate, LDH, CRP                                                                                                                       |
| β2 Microglobulin                     |                                                                                                                                                                                                                                                                                                                   |

|                                              |                                                                                                                                                                                                                                                                                                                                                                                                          |
|----------------------------------------------|----------------------------------------------------------------------------------------------------------------------------------------------------------------------------------------------------------------------------------------------------------------------------------------------------------------------------------------------------------------------------------------------------------|
| Myeloma Disease Assessment Laboratory | M-protein determination: 
 
• Serum protein electrophoresis and immunofixation
 
• Urine protein electrophoresis and immunofixation
 
• Serum free light chains and Hevylite test
 
• Serum quantitative immunoglobulins
 
 All of the above assessments are required at screening regardless of the disease classification.            |
| Bone Marrow Biopsy                    | Quantify percent myeloma cell involvement, obtain bone marrow aspirate for MRD analysis by NGS, and obtain bone marrow aspirate for conventional cytogenetics and fluorescent in situ hybridization. This is required at screening. For subjects who sign consent for correlative samples, an additional aspirate sample should be collected at screening. Calibration sample for MRD is required |
| CT-PET                                | A CT-PET must be performed to confirm MRD-negative disease per standard of care, at every time point when MRD is checked                                                                                                                                                                                                                                                                                 |
| Skeletal Survey                       | May be within 30 days of starting planned treatment (does not need to be repeated if within 30 days). Includes: lateral radiograph of the skull, anteroposterior and lateral views of the spine, and anteroposterior views of the pelvis, ribs, femora, and humeri, whole body MRI, or whole body CT.                                                                                                    |
| Neurotoxicity Assessment              | Includes Neurotoxicity Questionnaire ( Appendix 5 )                                                                                                                                                                                                                                                                                                                                      |
| QOL Assessment                        | Patient reported survey ( Appendix 6 )                                                                                                                                                                                                                                                                                                                                                   |
| Adverse Events                        | Only SAEs considered related to study procedure need to be reported.                                                                                                                                                                                                                                                                                                                                     |

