## 5 Patient Selection

### 5.1 Inclusion Criteria

Subjects must meet all of the following inclusion criteria to be eligible to enroll in this study. No enrollment waivers will be granted.

1. Newly diagnosed, previously untreated myeloma requiring systemic chemotherapy
  - Prior treatment of hypercalcemia or spinal cord compression or active and/or aggressively progressing myeloma with corticosteroids or lenalidomide or bortezomib-based regimens does not disqualify the patient (the treatment dose should not exceed the equivalent of 160 mg of dexamethasone in a 4-week period or not more than 1 cycle of PI/IMiD-based therapy).
2. Both transplant and non-transplant candidates are eligible
3. Diagnosis of symptomatic multiple myeloma as per current IMWG uniform criteria prior to initial treatment
4. Monoclonal plasma cells in the BM  $\geq 10\%$  or presence of a biopsy-proven plasmacytoma
5. Measurable disease, prior to initial treatment including any emergent treatment of myeloma. Measurable disease will be indicated by one or more of the following:
  - Serum M-protein  $\geq 1$  g/dL
  - Urine M-protein  $\geq 200$  mg/24 hours
  - If serum protein electrophoresis is felt to be unreliable for routine M-protein measurement, then quantitative immunoglobulin levels are acceptable

- Serum Freelite measurable disease as per current IMWG criteria
6. Bone marrow specimen will be required at study entry; available DNA sample from pre-induction BM will be used for calibration step for MRD evaluation by gene sequencing
  7. Males and females  $\geq 18$  years of age
  8. ECOG performance status of 0-1
  9. Adequate hepatic function, with bilirubin  $\leq 1.5 \times \text{ULN}$  and aspartate aminotransferase (AST) and alanine aminotransferase (ALT)  $\leq 3 \times \text{ULN}$
  10. ANC  $\geq 1.0 \times 10^9/\text{L}$ , hemoglobin  $\geq 8 \text{ g/dL}$ , platelet count  $\geq 75 \times 10^9/\text{L}$
  11. Calculated creatinine clearance (by Cockcroft-Gault)  $\geq 50 \text{ mL/min}$  or serum creatinine below  $2 \text{ g/dL}$
  12. FCBP must have 2 negative pregnancy tests (sensitivity of at least  $50 \text{ mIU/mL}$ ) prior to initiating lenalidomide. The first pregnancy test must be performed within 10-14 days before and the second pregnancy test must be performed within 24 hours before lenalidomide is prescribed for Cycle 1 (prescriptions must be filled within 7 days).

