### **6.3.5 Daratumumab Administration (Subcutaneous Injection)**

Daratumumab will be administered by subcutaneous (SC) injection as a fixed-dosed of 1800 mg by manual push over 3 to 5 minutes in the abdominal SC tissues in left/right locations, alternating between individual doses. The volume of the SC solution will be 15 mL for the 1800 mg dose. The dose of daratumumab will remain constant throughout the study.

As noted in the Schedule of Events, all subjects will be observed for 1 hour after the first dose of subcutaneous daratumumab during Cycle 1 Day 1 and, if deemed necessary by the treating investigator,

after subsequent injections (all patients will be switching from the IV formulation; there will be no new starts). If a subject experiences any significant medical event, then the treating investigator should assess whether the subject should stay overnight for observation. If the subject has not experienced a significant medical event but is hospitalized overnight only for observation, then the hospitalization should not be reported as a serious adverse event. Reasons for continued observation on subsequent daratumumab injections may include but are not limited to the following: subjects with a higher risk of respiratory complications (eg, subjects with mild asthma or subjects with COPD who have an FEV1 < 80% at screening or developed FEV1 <80% during the study without any medical history), subjects with injection-related reactions (IRRs) with first injection of study drug, or subjects with a decreased condition on day of dosing compared to the prior dosing day.

Patients with a history of obstructive pulmonary disorders may require additional post-infusion medications to manage respiratory complications. Consider prescribing short- and long-acting bronchodilators and inhaled corticosteroids for patients with obstructive pulmonary disorders.

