## **APPENDIX 7: Lenalidomide Pregnancy Risk Minimization Plan for Celgene Clinical Trials**

### **Lenalidomide Pregnancy Prevention Plan for Subjects in Clinical Trials**

The Pregnancy Prevention Plan (PPP) applies to all subjects receiving lenalidomide within a clinical trial. The following PPP documents are included:

1. The Lenalidomide Risks of Fetal Exposure, Pregnancy Testing Guidelines and Acceptable Birth Control Methods document (Section 0) provides the following information:

- Potential risks to the fetus associated with lenalidomide exposure
- Definition of female of childbearing potential (FCBP)/female not of childbearing potential (FNCBP)
- Requirements for counseling of all subjects receiving lenalidomide about pregnancy precautions and the potential risks of fetal exposure to lenalidomide
- Acceptable birth control methods for both female subjects of childbearing potential and male subjects receiving lenalidomide in the study
- Pregnancy testing requirements for subjects receiving lenalidomide who are FCBP

2. The Lenalidomide Education and Counseling Guidance Document for each gender (female and male; Section 2 and Section 3 respectively) must be completed and signed by a trained counselor at the participating clinical center prior to each dispensing of lenalidomide. A copy of this document must be maintained in the subject's records for each dispense.

3. The Lenalidomide Information Sheet (Section 4) will be given to each subject receiving lenalidomide. The subject must read this document prior to starting lenalidomide and each time the subject receives a new supply of lenalidomide.

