## **1.4. Pregnancy Testing**

Medically supervised pregnancy tests with a minimum sensitivity of 25 mIU/mL must be performed for FCBP.

Females of childbearing potential must have two negative pregnancy tests (sensitivity of at least 25 mIU/mL) prior to starting lenalidomide. The first pregnancy test must be performed within 10 to 14 days prior to the start of lenalidomide and the second pregnancy test must be performed within 24 hours prior to the start of lenalidomide. The subject may not receive lenalidomide until the study doctor has verified that the results of these pregnancy tests are negative.

Females of childbearing potential with regular or no menstrual cycles must agree to have pregnancy tests weekly for the first 28 days of study participation and then every 28 days while taking lenalidomide, at study discontinuation, and at Day 28 following the last dose of lenalidomide.

Females of childbearing potential with irregular menstrual cycles must agree to have pregnancy tests weekly for the first 28 days of study participation and then every 14 days while taking lenalidomide, at study discontinuation, and at Days 14 and 28 following the last dose of lenalidomide.

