## **1.5. Pregnancy Precautions for Lenalidomide Use**

### **1.5.1. Before Starting Lenalidomide**

#### **1.5.1.1. Female Subjects of Childbearing Potential**

Females of childbearing potential must have two negative pregnancy tests (sensitivity of at least 25 mIU/mL) prior to starting lenalidomide. The first pregnancy test must be performed within 10 to 14 days prior to the start of lenalidomide and the second pregnancy test must be performed within 24 hours prior to the start of lenalidomide. The subject may not receive lenalidomide until the study doctor has verified that the results of these pregnancy tests are negative.

Females of childbearing potential must use two reliable forms of contraception simultaneously, or practice complete abstinence (True abstinence is acceptable when this is in line with the preferred and usual lifestyle of the subject. Periodic abstinence [e.g. calendar, ovulation, symptothermal or post-ovulation methods] and withdrawal are not acceptable methods of contraception.) from heterosexual contact for at least 28 days before starting lenalidomide.

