6. Systolic and diastolic blood pressure, pulse, respiration, temperature approximately 1 hour before dosing.
7. 24 hour urine total protein, urine protein electrophoresis (UPEP), and urine protein immunofixation. For subjects whose disease is being monitored through UPEP, additional post baseline 24-hour urine collections are required as indicated.
8. For subjects whose disease is being monitored through UPEP, additional post baseline 24-hour urine collections are required as indicated.
9. Hemoglobin, hematocrit, WBC with complete differential, RBCs, platelet count. Results must be reviewed before dosing.
10. Cycles 1 and 2 only and subsequent cycles as clinically indicated or per institutional standard of care.
11. Full serum chemistry panel at Screening, Days 1, 8, and 15 of Cycles 1-8, and Day 1 of Cycles 9+: sodium, potassium, chloride, bicarbonate, BUN, creatinine, glucose, uric acid, total protein, albumin, calcium, phosphorus, magnesium, total bilirubin, alkaline phosphatase, ALT, AST, LDH. Results must be reviewed before dosing in Cycles 1 and 2.
12. Abbreviated serum chemistry panel on Days 2, 9, and 16 of Cycles 1 and 2 only or as clinically indicated (e.g., risk factors for tumor lysis syndrome): sodium, potassium, chloride, bicarbonate, BUN, creatinine, glucose, uric acid.
13. Pregnancy tests for females of childbearing potential. A female of childbearing potential (FCBP) is a sexually mature female who: 1) has not had a hysterectomy or bilateral oophorectomy; or 2) has not been naturally post-menopausal for at least 24 consecutive months (i.e., menses within the preceding 24 months).
14. Pregnancy tests must occur within 10-14 days and again within 24 hours prior to prescribing lenalidomide (prescriptions must be filled within 7 days. FCBP with regular or no menstruation must have a pregnancy test weekly for the first 28 days and then every 28 days while on therapy (including breaks in therapy); at discontinuation of lenalidomide and at Day 28 post the last dose of lenalidomide. Females with irregular menstruation must have a pregnancy test weekly for the first 28 days and then every 14 days while on therapy (including breaks in therapy), at discontinuation of lenalidomide and at Day 14 and Day 28 post the last dose of lenalidomide (see Appendix 7 for Risks of Fetal Exposure, Pregnancy Testing Guidelines and Acceptable Birth Control Methods).

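### The eligibility and screening text accepts pre-lenalidomide pregnancy tests at 50 mIU/mL, but the pregnancy prevention plan in Appendix 7 requires 25 mIU/mL

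*Protocol*

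**What the plan says.** Two parts of the protocol body set the sensitivity of the two pregnancy tests that a female of childbearing potential (FCBP) needs before lenalidomide.

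- Section 5.1, criterion 12, opens "FCBP must have 2 negative pregnancy tests (sensitivity of at least" and gives the figure as 50 mIU/mL.
- Section 6.1.1, Pregnancy Test, says "FCBP must have two negative pregnancy tests (sensitivity of at least 50 mIU/mL) prior to starting study treatment".

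Appendix 7 sets a different figure.

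- Section 1.4 says "Medically supervised pregnancy tests with a minimum sensitivity of 25 mIU/mL must be performed for FCBP", and its next paragraph repeats 25 mIU/mL for the two tests before lenalidomide.
- Section 1.5.1.1 says "Females of childbearing potential must have two negative pregnancy tests (sensitivity of at least 25 mIU/mL) prior to starting lenalidomide".

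Appendix 7 also states its own scope: "The Pregnancy Prevention Plan (PPP) applies to all subjects receiving lenalidomide within a clinical trial". Lenalidomide is part of the regimen for every subject, so the appendix binds all FCBP in this trial.

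**The concern.** The protocol gives two detection thresholds for one safety check, and the weaker one stands in the eligibility criteria. Section 5.3.1 has sites submit an eligibility checklist with source documents for each criterion, so a 50 mIU/mL test would be accepted at registration. Neither criterion 12 nor section 6.1.1 refers the reader to Appendix 7.

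A site that works from the eligibility text alone could therefore breach the prevention plan. It could also miss an early pregnancy with hCG between 25 and 50 mIU/mL. Appendix 7, section 1.1, describes lenalidomide as a chemical relative of thalidomide, reports malformations in monkey offspring, and does not exclude a teratogenic effect in humans. This is a matter of safety and eligibility; no estimate or decision rule depends on it.

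**Working it through.** No formula applies, so the check sets the texts side by side and asks which tests each would accept.

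| Place in protocol | Tests covered | Required sensitivity |
|---|---|---|
| 5.1, criterion 12 | Two negative tests before lenalidomide | 50 mIU/mL |
| 6.1.1, Pregnancy Test | Two negative tests before study treatment | 50 mIU/mL |
| Appendix 7, 1.4, first paragraph | Pregnancy tests in FCBP | 25 mIU/mL |
| Appendix 7, 1.4, second paragraph | Two negative tests before lenalidomide | 25 mIU/mL |
| Appendix 7, 1.5.1.1 | Two negative tests before lenalidomide | 25 mIU/mL |
| 6.1.2, 6.1.3, 6.2.2.1; Appendix 8 footnotes 13 and 14 | Various | None stated |

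**Step 1: are these the same tests?** Yes. Both sets of text describe a first test 10 to 14 days ahead and a second test tied to a 24-hour limit.

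**Step 2: are both figures current?** Yes. Both stand in operative text, and neither comes from a summary of changes.

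**Step 3: which tests does each text accept?** Read each figure as a detection limit, where lower is more sensitive, and call the limit L.

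- Body text: L ≤ 50 mIU/mL.
- Appendix 7: L ≤ 25 mIU/mL.
- Accepted by the body and refused by Appendix 7: 25 < L ≤ 50 mIU/mL.
- Accepted by both: L ≤ 25 mIU/mL.

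**Step 4: is there a rule of precedence?** No explicit one. Appendix 8 footnote 14 points to Appendix 7 but states no sensitivity and does not rank the two texts.

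**Step 5: how many tests could be involved?** The planned enrolment is 45 subjects with two pre-treatment tests each, so the ceiling is 45 × 2 = 90. That would need every subject to be an FCBP, in a trial open to men and women aged 18 or over. The protocol gives neither the number of FCBP nor the assays that sites use, so the true number cannot be estimated beyond saying that it is lower.

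**The case against.** The strongest reply is that the two rules stack and do not collide. Each sets a minimum, and a 25 mIU/mL test meets both, so no site has to break one rule to keep the other. In effect the stricter rule governs anyway: Appendix 7 applies to everyone on lenalidomide, and it withholds the drug until the study doctor has verified negative results. Schedule footnote 14 also directs sites there ("see Appendix 7 for Risks of Fetal Exposure, Pregnancy Testing Guidelines and Acceptable Birth Control Methods"). Contraception and repeat testing add further protection. Harm would need a site to overlook a mandatory appendix and also to use a less sensitive assay, and the protocol shows neither. Section 6.3.5 adds that "all patients will be switching from the IV formulation; there will be no new starts", so most or all of the pre-treatment tests may already have been done.

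Most of this stands, and it is why the practical risk is limited. It does not remove the inconsistency. The Appendix 7 check asks the study doctor to verify that the results are negative; a negative result from a 50 mIU/mL test that met criterion 12 would look acceptable unless someone noticed the other figure. The remark about no new starts sits in the section on subcutaneous daratumumab, while this version still carries full eligibility, screening and registration text.

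A further reply is that correcting the sensitivity leaves a difference in timing. The body ties the second test to the prescribing of lenalidomide, whereas Appendix 7 ties it to the start of the drug. That is correct, but it is a separate matter and does not weaken the case for correcting the sensitivity.

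**Conclusion.** The point holds: criterion 12 and section 6.1.1 state a looser sensitivity than the pregnancy prevention plan that binds the same subjects for the same two tests. The affected range is detection limits above 25 and up to 50 mIU/mL, and at most 90 pre-treatment tests could fall in it. This rests on two assumptions: that the stated figures are detection limits, and that some site might use an assay in that range, which the protocol neither shows nor excludes.

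The correction should be made because it concerns an operative eligibility figure and patient safety. Given the safeguards in Appendix 7, the practical risk is limited. Sample size, primary endpoint and analysis are unaffected.

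**What to change.** In section 5.1, criterion 12, and in section 6.1.1, Pregnancy Test, replace 50 mIU/mL with 25 mIU/mL, to match Appendix 7, sections 1.4 and 1.5.1.1. The other pregnancy-test texts (6.1.2, 6.1.3, 6.2.2.1 and schedule footnotes 13 and 14) state no sensitivity and need no change on this point.

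The cost is one figure in two places, with no added tests or visits.
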